### **5.3 Study Visit Window**

Scheduled Vaccination and Follow up Visits will be treated as within the study protocol, if performed plus or minus 7 days from the study day specified in the protocol. If a subject has a fever at a Vaccination Visit, then the Visit can be rescheduled by up to four weeks without recording a protocol violation.

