## **2. STUDY OBJECTIVES**

### **2.1 Primary Endpoints:**

- Seroconversion and seroprotection rates and mean GMT increases in haemagglutination inhibition titres 21-28 days post-immunisation for each of the three included vaccine strains

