### **2.2 Secondary Endpoints:**

- Pain scores and subject satisfaction with needleless injection device
- Anti-influenza T-cell responses and kinetics
- Persistence of anti-HA antibody levels and T-cell immunity to influenza
- Cross-protection against drifted influenza strains
- Study of immune cell gene correlates of vaccine immunogenicity and reactogenicity
- Influenza plasmablast frequency at day 7 post-immunization

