#### **Day 7**

Visit to provide blood samples specifically for measurement of influenza plasmablast responses

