#### **Days 14 and 21- Substudy subjects only**

Visit to provide blood samples specifically for measurement of B- and T-cell responses. This visit will only involve the subset of subjects who specifically consent to be in the substudy that will involve weekly attendance for 4 weeks for collection of blood.

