#### **Day 28 – Final Visit (All subjects)**

Final study visit to provide blood samples and for collection of patient diary. Subjects will have their injection site examined and have any adverse events recorded.

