**Immune response assays.**

Blood samples will be drawn for the evaluation of influenza antibody titres of all the individuals immediately prior to immunization, and 7 days and 4 weeks post immunization. Those subjects who consent to be in the Substudy will have blood taken weekly for 4 weeks post-immunisation for analysis of B- and T-cell responses to influenza and control antigens.

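### The uniform ±7-day visit window lets the Day 7 plasmablast sample fall anywhere from Day 0 to Day 14, and the final sample up to a week past the 21-28 day primary endpoint

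*Protocol*

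**What the plan says.** Protocol Section 5.3 sets one tolerance for the whole trial. A visit of either kind, for vaccination or for follow-up, is compliant "if performed plus or minus 7 days from the study day specified in the protocol". The only exception it gives is postponement of a vaccination visit for fever.

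The sampling times to which this applies are:

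- **Day 7.** Section 4.1.1 describes this as a "Visit to provide blood samples specifically for measurement of influenza plasmablast responses". Section 2.2 lists the endpoint as "Influenza plasmablast frequency at day 7 post-immunization".
- **Days 14 and 21, substudy subjects only.** Section 4.1.1: "Visit to provide blood samples specifically for measurement of B- and T-cell responses".
- **Day 28, all subjects.** Section 4.1.1: "Final study visit to provide blood samples and for collection of patient diary".
- **Antibody titres.** The immune response assay text in Section 8.7.2 schedules these "immediately prior to immunization, and 7 days and 4 weeks post immunization".

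Section 2.1 defines the primary antibody endpoint on "haemagglutination inhibition titres 21-28 days post-immunisation for each of the three included vaccine strains".

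Section 9.3(c) counts a visit as a protocol violation only when it falls outside the window. Section 9.2.2 admits to the per-protocol population anyone with a dose, a baseline titre and at least one later titre, with no condition on when the later sample was drawn.

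**The concern.** A ±7-day tolerance is as wide as the gap between successive post-vaccination visits in the weekly schedule. Two of the protocol's own endpoints are tied to time more tightly than that.

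The first is the plasmablast endpoint. It is defined at a single day, and the Day 7 visit is described as existing for that measurement. The window nevertheless opens on the day of vaccination, when no response to the vaccine can yet be present, and closes on the nominal day of the next substudy visit. Samples from quite different stages of the response can all carry the Day 7 label. The weekly B- and T-cell kinetics in the substudy have the same weakness.

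The second is the primary endpoint. The Day 28 visit is the only all-subject visit that can supply the 21-28 day antibody sample, and its window runs a week past the end of that interval. A sample drawn on Days 29-35 complies with Section 5.3 but does not meet Section 2.1, and the protocol does not say how it is to be treated.

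**Working it through.** No sample-size or error-rate formula applies; the check is interval arithmetic.

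**Inputs.** Tolerance w = 7 days (Section 5.3). Nominal days d = 7, 14, 21 and 28 (Section 4.1.1). Primary interval 21-28 days (Section 2.1). Plasmablast endpoint at day 7 (Section 2.2).

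**Step 1: permitted window = [d − w, d + w].**

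| Visit | Who attends | Calculation | Permitted days |
|---|---|---|---|
| Day 7 | All | 7 ± 7 | 0-14 |
| Day 14 | Substudy | 14 ± 7 | 7-21 |
| Day 21 | Substudy | 21 ± 7 | 14-28 |
| Day 28 | All | 28 ± 7 | 21-35 |

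**Step 2: Day 7 against its endpoint.** The endpoint names one day; the window allows 14 − 0 + 1 = 15 days, the first of which is the day of vaccination.

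**Step 3: overlap.** For substudy subjects the Day 7 and Day 14 windows share Days 7-14, the Day 14 and Day 21 windows share Days 14-21, and the Day 21 and Day 28 windows share Days 21-28. For everyone else the only windows are 0-14 and 21-35, which do not overlap.

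**Step 4: final visit against the primary endpoint.**
- Permitted days: 35 − 21 + 1 = 15.
- Inside the 21-28 interval: 28 − 21 + 1 = 8.
- Outside it: 15 − 8 = 7, namely Days 29-35.
- The lower limit agrees exactly (28 − 7 = 21). The mismatch is on the late side only.

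**Step 5: does another section catch these samples?** Under Section 9.3(c), a plasmablast sample on Day 0 or Day 14, or a final sample on Day 35, is not a violation. Under Section 9.2.2, a Day 29-35 titre does not remove the subject from the per-protocol population. Neither section flags or excludes the samples.

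**Step 6: what would remove the conflict.**
- Visits 7 days apart have non-overlapping whole-day windows when 2w < 7, so w is at most 3. With ±2 at Day 7 and ±3 afterwards, the windows are 5-9, 11-17, 18-24 and 25-31.
- The final-visit window and the primary interval coincide either if the interval becomes Days 21-35 with the window left at ±7, or if the window becomes −7/+0, that is Days 21-28.
- In both cases a Day 21 ±3 window (18-24) still meets the final-visit window on Days 21-24. The substudy cellular samples therefore need their own ±3 limit at Day 28 as well, or assignment by actual day.

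**The case against.** The strongest reply is that Section 5.3 is a compliance rule and not an analysis rule. It says when a visit counts as within protocol. It does not say that a Day 0 or Day 14 sample will be analysed as the Day 7 value, and Section 2.2 still defines that endpoint at day 7. Analysis windows are commonly left to a statistical analysis plan, which may exist here. This stands in part: it is why the point concerns what the protocol permits, not what the analysis will necessarily do. It does not dispose of the point. The rule governs when sites draw blood, and an analysis plan can exclude a mistimed plasmablast sample but cannot recover the one that should have been drawn. The conflict between Sections 2.1 and 5.3 is between two stated rules, not an omitted detail.

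Other limits also stand:

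- **Overlap.** It concerns substudy visits only. A reader might infer that one Day 14 sample could be counted for three visits. Nothing in the protocol allows that; each visit is scheduled separately and in order.
- **Direction of harm.** A reader might infer that loose timing could reverse a difference between arms. The protocol does not support this. One window applies to all randomised arms, and subjects and laboratory are blinded (Section 5.2). Timing scatter unrelated to arm adds noise and tends to dilute a difference.
- **Competing primary samples.** A reader might infer that substudy subjects have both a Day 21 and a Day 28 primary titre. Section 8.7.2 schedules antibody titres at baseline, 7 days and 4 weeks only, and the Day 14 and 21 blood is for cellular responses.
- **Late titres.** Nothing in the protocol shows that titres on Days 29-35 differ materially from those on Day 28.

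**Conclusion.** The point holds as a conflict between a stated visit rule and stated endpoints, and it should be corrected. The Day 7 plasmablast sample is compliant over 15 days (0-14) for an endpoint defined at one day. The final sample is compliant on 7 days (29-35) out of 15 that fall outside the primary interval. The weekly windows of substudy subjects overlap.

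The Day 7 part matters more in practice, because a mistimed sample there cannot be repaired later. The primary-endpoint part is a single unreconciled upper limit.

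The likely consequence is noise and dilution in the time-specific comparisons, assuming that visit timing is unrelated to arm. The size of the effect on plasmablast counts or titres cannot be computed, because the protocol gives neither expected attendance times nor response curves. The figures above describe what is permitted, not how often it will happen.

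**What to change.** Replace the uniform window in Section 5.3 with visit-specific windows.

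1. **Day 7 plasmablast visit.** Set a narrow window that excludes the day of vaccination and does not reach Day 14. A width of ±1 to ±2 days is a proposal; the protocol gives no basis for deriving an exact figure. Leave out-of-window samples out of the Day 7 analysis.
2. **Substudy B- and T-cell samples.** Use at most ±3 days at each weekly visit, including the Day 28 cellular sample, and analyse by actual day since vaccination.
3. **Primary antibody sample.** Reconcile Section 2.1 with Sections 4.1.1 and 5.3. The simplest route is to restate the primary interval as Days 21-35. The alternative is to end the final-visit window at Day 28.
4. **Section 9.3(c).** Refer to the new windows, so that the violation listing picks up mistimed samples.

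The cost is protocol wording, with no change to sample size or treatment. More visits will be recorded as out of window, and some Day 7 samples will be lost to that analysis; how many cannot be estimated from the protocol. Restating the interval as Days 21-35 accepts a wider spread of times for the primary titre, while ending the window at Day 28 makes a final visit one day late a violation.

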### **5.4 Safety Monitoring Board**

Given the short duration of this study and the fact that just a single immunization will be given on study day 0, a safety monitoring board (SMB) is not deemed suitable for this study. The Principal Investigator will monitor all serious adverse events and if considered to be related to study medication this will be notified to the ethics committee.

## **6. STUDY POPULATION**

The study population will comprise up to 400 subjects 18 years and older, who fulfil the inclusion criteria, do not meet any of the exclusion criteria, and who have given informed consent.

### **6.1 Inclusion criteria**

- Male or female
- Age 18 years or over
- Able to provide written informed consent
- Willing and able to comply with the protocol for the duration of the study.

### **6.2 Exclusion criteria**

- History of vaccination with the 2012 seasonal influenza vaccine
- History of serious vaccine or egg allergy
- Women of childbearing potential, unless using a reliable and appropriate contraceptive method, specifically oral contraceptive pill, IUD or mechanical barrier device.
- Pregnant or lactating women.
- Receipt of another investigational agent within 14 days preceding initiation of treatment.
- Any other serious medical, social or mental condition which, in the opinion of the investigator, would be detrimental to the subjects or the study.

### **6.3 Replacement policy**

Individuals dropping out of the study prior to Visit 3 will be replaced at the discretion of the Principal Investigator.

## **7. TREATMENTS**

### **7.1 Treatments administered**

Study subjects will receive the vaccine by intramuscular injection into the deltoid muscle using a needle and syringe or needleless injector device.

### **7.2 Identity of investigational product**

The influenza vaccine will be formulated as either 2012 seasonal TIV or the same TIV formulated with 10mg or 20 mg Advax™ adjuvant.

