The 2012 seasonal influenza vaccine that will form the basis of this study is approved by the TGA. In this study, Advax™ adjuvant at either 5mg or 10mg will be formulated with the 2012 seasonal influenza vaccine, to allow us to confirm whether the reduced adjuvant dose delivers an equivalent anti-influenza antibody response. The rationale for testing a lower adjuvant dose is supported by data from a previous trial of a hepatitis B vaccine where Advax™ adjuvant at 5mg and 10mg doses was shown to be effective. If successful, this study would allow us to minimise the adjuvant dose and thereby maximise adjuvant availability, which could otherwise be a limiting factor, for example in an influenza pandemic where speed of production is critical.

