### **1.2.2 Rationale for schedule and route of administration**

The goal for influenza vaccination is to achieve a protective immune response in a minimum time frame and with the simplest dosing schedule. Animal data using several different models show that there is an increase in both the magnitude of the antibody response as the dose of antigen and adjuvant is increased to a critical levels but beyond this level the antibody response plateaus whilst the risk of adverse reactions continues to rise in a dose dependent manner. Hence it is critical to perform dose ranging studies to identify this “sweet spot” in the antigen and adjuvant dose response. Whilst previous clinical studies have compared different antigen doses, a fixed 20mg dose of Advax™ adjuvant was used. Hence there remains a need to be addressed in this study to now test different doses of adjuvant while keeping the dose of antigen fixed.

New technology has made available a needleless injection that delivers the vaccine through an intramuscular route without the use of a needle, instead utilising a spring powered energy source to inject liquid directly through the skin. The PharmaJet injector

employs a single-use, sterile, auto-disable needle-free syringe that results in an arguably superior injection experience and sensation compared to needle-bearing syringes. This device is FDA approved. Based on the above, we will trial a one dose regime of seasonal influenza vaccine delivered using standard needle and syringe or the PharmaJet needleless injector in a 1:1 ratio for all groups. This will enable us to assess patient satisfaction when using a needleless injector compared to needle-bearing vaccination administration.

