### **1.2.3 Rationale for selection of doses**

Currently available commercial seasonal influenza vaccines contain 15 micrograms of influenza haemagglutinin (HA) from the three influenza virus serotypes (two A serotypes and one B serotype) approved by TGA for that particular year's vaccine. This equates to a total of 45 micrograms of HA per vaccine in 0.5mls volume. As the needleless injector has a capacity of 0.5mls this means that it can inject the full dose of influenza HA. When formulated with Advax for use in the needleless injector, this will reduce the dose of influenza HA by approximately 20% in order to keep the volume to 0.5mls. However, we have previously shown that much greater HA dose reductions (3-10 fold) had little impact on the immunogenicity of influenza vaccine when combined with Advax™ adjuvant.

We have previously demonstrated in other clinical studies that Advax™ adjuvant is safe and effective in the dose range of 5 to 20mg although only the 20mg dose has been tested with influenza vaccines. In this study, we wish to test whether the same benefits can be achieved from a lower 5mg or 10mg dose of Advax™. This would reduce the dose of adjuvant required for each vaccine and thereby provide benefits in terms of reducing the cost of each vaccine and increasing adjuvant availability, for example in a pandemic, where a large number of vaccine doses might be required in a short space of time

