### **5.2 Choice of control groups and blinding**

This is a randomized, controlled Phase 2 study. A total of up to 400 subjects will be recruited for the study, and randomly assigned on a one to one to one basis (1:1:1) to standard TIV, TIV + Advax 5mg or TIV + Advax 10mg. All subjects will also be randomised on a 1:1 basis to receive the immunisation via needle and syringe or Pharmajet needleless injector device. There will therefore be 6 subgroups in total.

As the vaccine containing Advax is a cloudy white colour whereas TIV is a clear solution, it is not possible for the staff administering the vaccine to be blinded. Subjects will be blinded and will not be informed which vaccine they receive. Similarly, where a trial adverse effect requires assessment, this will be performed by a blinded adjudicator. All laboratory tests will be performed blinded.

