### **7.3 Supply, packaging and labelling**

All vaccines will be stored at 4°C. Each vial of study drug will have a pre-printed label including the following information: study number, bulk batch number, and volume. A space is also provided for the person administering the drug to enter the individual's ID number and initials at the time of administration. The vial will be labelled for Clinical Trial Use Only.

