### **7.4 Preparation**

A minimum of 30 minutes before administration the vaccine will be transferred from 4°C storage to room temperature for temperature equilibration. Standard TIV will be supplied in a pre-packaged syringe with needle as supplied by the manufacturer. For subjects receiving the adjuvanted vaccine, the adjuvant will be supplied and mixed with vaccine as per the vaccine administration SOP. The vaccine is mixed by repeated inversion before the complete contents of the vial are aspirated into either a new 1ml syringe or the needleless injector device disposable cartridge. The formulated vaccine can be kept at room temperature for 8 hours. Before administration, the adjuvanted vaccine syringe/cartridge should be inverted a number of times to ensure even mixing of

the adjuvant. Standard influenza vaccine is a clear solution whereas the vaccine containing adjuvant is a cloudy white colour.

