### **9.10 Randomisation procedure**

Random allocation sequences will be generated by an independent source. . Randomisation codes will be held independently to the site. To randomise a subject the investigator or study co-ordinator will use an on-line interface to enter subject initials and date of birth. On entering this data, they will be issued with the next available randomisation code for the particular randomisation block or category to which the entered subject belongs, e.g. with or without Advax, 10mg or 20mg etc.

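### Section 7.2 defines the adjuvanted vaccine as 10 mg or 20 mg Advax, but the randomised arms in Section 5.2 are 5 mg and 10 mg

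*Protocol*

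**What the plan says.** The Protocol gives the study's Advax dose in five places, and they do not agree.

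- Section 5.2 (control groups and blinding) allocates subjects 1:1:1 "to standard TIV, TIV + Advax 5mg or TIV + Advax 10mg".
- Section 1.1 (background) says that "adjuvant at either 5mg or 10mg will be formulated with the 2012 seasonal influenza vaccine".
- Section 1.2.3 (dose selection) says "we wish to test whether the same benefits can be achieved from a lower 5mg or 10mg dose of Advax".
- Section 7.2 (identity of investigational product) says the vaccine is either plain TIV or "the same TIV formulated with 10mg or 20 mg Advax".
- Section 9.10 (randomisation procedure) illustrates the randomisation categories with "e.g. with or without Advax, 10mg or 20mg etc".

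The 20 mg dose also appears as history. Section 1.2.2 notes that, while "previous clinical studies have compared different antigen doses, a fixed 20mg dose of Advax" was used. Section 1.2.3 adds that 20 mg is the only dose so far tested with influenza vaccine.

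The rest of Section 7 gives no other adjuvant dose. Section 7.3 lists a "pre-printed label including the following information: study number, bulk batch number, and volume". Section 7.4 says "the adjuvant will be supplied and mixed with vaccine as per the vaccine administration SOP".

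**The concern.** Adjuvant dose is the factor this trial sets out to study. Section 1.1 states the aim as comparing doses below those tested before, to find the smallest one that gives full enhancement. The section that defines the product nevertheless omits the lower planned dose and includes the dose the trial is meant to improve on.

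If product were prepared to Section 7.2, the 5 mg formulation would not exist and could not be assessed. The 20 mg formulation would repeat a dose already used with influenza antigen.

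There is a second, smaller consequence. Section 7.8.1 treats any dose other than the one the protocol shows as a violation, and Section 11.4 does not permit doses that the protocol does not schedule. With 5 mg in some sections and 20 mg in others, a correct 5 mg dose conflicts with 7.2, and an erroneous 20 mg dose could be defended by citing it.

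**Working it through.** No power or sample-size formula applies. The check is to set the dose statements side by side and count the subjects affected.

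**1. Study doses by section**

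| Section | Role of the text | Advax doses |
|---|---|---|
| 1.1 | Background and aim | 5 mg, 10 mg |
| 1.2.3 | Dose rationale | 5 mg, 10 mg |
| 5.2 | Randomised arms | 5 mg, 10 mg |
| 7.2 | Product identity | 10 mg, 20 mg |
| 9.10 | Example of randomisation categories | 10 mg, 20 mg |

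The two pairs share only 10 mg. The 5 mg arm in 5.2 has no product in 7.2, and the 20 mg product in 7.2 has no arm in 5.2.

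**2. Which pair is intended**

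Section 1.1 says the doses are to be lower than those tested before. Sections 1.2.2 and 1.2.3 put the earlier influenza dose at 20 mg. Both 5 mg and 10 mg satisfy that aim; 20 mg does not. The arm definition agrees with the rationale, so 7.2 and 9.10 are the sections in error. Neither is an amendment log or a description of superseded text, and no redaction accounts for the difference.

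**3. Size of the conflict**

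Section 9.7 plans 6 groups of 65, so 6 × 65 = 390 subjects. Each formulation covers two groups (needle and needleless).

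- *Narrower reading: the shared 10 mg arm is unaffected.* The mismatch is 5 mg against 20 mg, a ratio of 20/5 = 4. It affects 2 × 65 = 130 subjects, and 130/390 = 33.3%. If 400 enrol at 1:1:1, it affects 400/3 ≈ 133.
- *Wider reading: the pairs correspond low to low and high to high.* The ratios are 10/5 = 2 and 20/10 = 2, so both adjuvanted formulations are doubled. That affects 4 × 65 = 260 subjects, and 260/390 = 66.7%.

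The text does not show which correspondence anyone would apply in practice. The first is the smaller claim.

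**4. Whether another part of Section 7 catches the error**

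The label items in 7.3 do not include adjuvant dose. Section 7.4 refers to an SOP for mixing, which is not shown. Someone who turned to the treatment section alone would find only the 10 mg and 20 mg figures.

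**The case against.** The strongest reply is that this is a drafting slip that any careful reader would resolve. Sections 1.1, 1.2.3 and 5.2 agree, and the reason for preferring doses below 20 mg is explained. The arms, sample size and analyses do not change. The consequences above follow only if 7.2 is preferred to 5.2, and the SOP that governs mixing may carry the right doses. For the violation rule, the natural reference is the dose of the arm to which the subject was randomised, so 20 mg given to a 5 mg subject would be a violation on any sensible reading. Section 9.10 offers only an example, and an example does not set a dose.

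Much of that stands. The intent is clear, no operational effect can be shown from the document, the violation-rule argument is secondary, and 9.10 is weak evidence on its own. What the reply does not remove is a wrong dose in the section that defines the product. The repetition in 9.10 also makes a single mistyped figure less likely, and gives a reason to check the documents derived from the protocol.

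**Conclusion.** The concern holds. Section 7.2 states the wrong adjuvant doses, and the 9.10 example repeats them. The intended doses are 5 mg and 10 mg.

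The size is at least a four-fold mismatch for one of three formulations (130 of 390 planned subjects), or a two-fold mismatch for both adjuvanted formulations (260 of 390) if the pairs are matched in order. These figures count subjects in arms whose product definition is wrong; they do not estimate an effect on the results. They assume the 6 × 65 plan in Section 9.7.

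No actual misdosing is alleged, since the SOP is not available. No new safety hazard is claimed either, because Section 1.2.3 reports 5 to 20 mg as safe in earlier studies. No loss of concealment is claimed: Section 9.10 limits the inputs to initials and date of birth and holds the codes away from the site.

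The correction is still required, because dose is the experimental variable and 7.2 is the only statement of it in Section 7.

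**What to change.** 1. In Section 7.2, replace 10 mg or 20 mg with 5 mg or 10 mg.
2. In Section 9.10, correct the example to the same pair. It would be cleaner, though optional, to delete the treatment examples and state that the issued code assigns one of the six formulation-by-device arms.
3. Check the vaccine administration SOP cited in Section 7.4 and the randomisation-system specification against Section 5.2, and correct either if it carries 10 mg and 20 mg.

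The cost is two wording corrections in a protocol amendment and one document check. Sample size, arms and analyses are unchanged.

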## **FULL PROTOCOL**

### **1. INTRODUCTION**

#### **1.1. Background**

Influenza is a highly contagious and potentially deadly disease that can be spread through coughing or sneezing. It is caused by a virus and is not the same as a common cold. It can cause serious and debilitating complications such as pneumonia, especially in the elderly, young children and those with chronic disease.

The current study is designed to establish the safety and efficacy of the standard commercial trivalent inactivated influenza vaccine (TIV) when formulated with a range of adjuvant doses. We have shown in previous studies that addition of Advax™ adjuvant with various seasonal (TIV) or pandemic (H1N1/2009) influenza, or hepatitis B antigens improved the immunogenicity of these vaccines as assessed by higher antibody titres. This is the basis for extending study of Advax™-adjuvanted influenza vaccine to compare adjuvant doses lower to those previously tested and thereby identify the minimum adjuvant dose required for maximal vaccine enhancement.

Seasonal influenza vaccines are currently administered by intramuscular injection using a syringe and needle approach. New technology has made available a needleless injection system that is able to deliver the vaccine utilising a spring powered energy source to create a fine high velocity jet of liquid that directly penetrates through the skin without the use of a needle. The PharmaJet injector which is already approved for human use by the US Food and Drug Administration (FDA) employs a single-use, sterile, auto-disable needle-free cartridge which results in an superior injection experience for children and needle phobic subjects compared to use of needle-bearing syringes. This technology offers major advantages for both administrator and recipient over existing needle injection approaches and hence we plan to randomise trial subjects to receive their vaccine through either the PharmaJet device or needle and syringe, thereby allowing us to assess the influence on patient satisfaction and comfort of receiving their influenza vaccine through a needleless device.

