### **7.8 Criteria for dose modification, dose escalation or vaccine discontinuation**

### **7.8.1 Dose modification**

The dose administered should always be in accordance with the protocol. If a dose other than that shown in the protocol is administered then this should be recorded as a protocol violation.

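### Section 7.2 and the example in section 9.10 give the Advax doses as 10 mg and 20 mg, but the trial randomises to 5 mg and 10 mg

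*Protocol*

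**What the plan says.** The protocol gives two sets of adjuvant doses.

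- **5 mg and 10 mg.** Section 5.2 sets the randomised formulations as "standard TIV, TIV + Advax 5mg or TIV + Advax 10mg", allocated 1:1:1 and crossed 1:1 with needle or needleless injector. Section 1.1 names the same two doses for the 2012 vaccine. Section 1.2.3 says "we wish to test whether the same benefits can be achieved from a lower 5mg or 10mg dose of Advax".
- **10 mg and 20 mg.** Section 7.2 defines the product as standard TIV or "the same TIV formulated with 10mg or 20 mg Advax". Section 9.10 illustrates the randomisation categories as "with or without Advax, 10mg or 20mg etc".

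Three other statements bear on which set is meant. Section 1.2.3 says that "only the 20mg dose has been tested with influenza vaccines". Section 1.2.2 says that earlier clinical studies varied the antigen dose at a fixed 20 mg of Advax. Section 1.1 says that the study will compare doses below those tested before.

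Section 7.8.1 ties compliance to the stated dose: "If a dose other than that shown in the protocol is administered then this should be recorded as a protocol violation".

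**The concern.** Section 7.2 is where a reader looks for what is to be given, and its doses do not match the randomised arms. The difference cannot be put down to rounding or to a change of units: one set contains 5 mg and no 20 mg, the other contains 20 mg and no 5 mg.

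Two things are at stake. First, section 7.8.1 defines a violation by reference to the dose shown in the protocol, and the protocol shows two sets. Whether a 5 mg or a 20 mg injection is compliant depends on which section is read, and section 11.4 does not permit unscheduled doses. Second, if 7.2 were followed, no subject would receive 5 mg and one arm would repeat the dose already studied with influenza vaccine. The low-dose question that motivates the trial would then go unanswered.

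The label contents listed in section 7.3 (study number, bulk batch number, volume) do not include the adjuvant dose, so the label as described would not reveal a mismatch.

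**Working it through.** **Step 1. The dose statements side by side (Protocol).**

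| Section | Role of the text | Advax doses |
|---|---|---|
| 1.1 Background | what will be formulated | 5 mg, 10 mg |
| 1.2.3 Rationale for doses | what will be tested | 5 mg, 10 mg |
| 5.2 Control groups and blinding | randomised arms | 5 mg, 10 mg |
| 7.2 Investigational product | product definition | 10 mg, 20 mg |
| 9.10 Randomisation procedure | example of categories | 10 mg, 20 mg |

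With the control, the sets are {0, 5, 10} mg and {0, 10, 20} mg. They share 0 and 10 mg. The remaining dose is 5 mg in one set and 20 mg in the other, a fourfold difference.

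**Step 2. Which set is intended.** Sections 1.2.2 and 1.2.3 make 20 mg the dose already used with influenza vaccine, and sections 1.1 and 1.2.3 call the trial doses lower. A 20 mg arm does not fit that rationale; 5 mg and 10 mg do. Section 5.2 therefore carries the intended doses, and 7.2 and 9.10 need correction.

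**Step 3. The plan's group size (section 9.7).** The inputs are a minimum of 50 evaluable subjects per group and 20% drop-out.

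- 50 / (1 − 0.20) = 62.5, rounded up to 63 per group. The plan uses 65, which is consistent with this.
- 65 × 0.80 = 52, at or above the minimum of 50.
- 6 × 65 = 390, within the ceiling of 400.

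None of these figures uses the adjuvant dose, so correcting it leaves them unchanged.

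**Step 4. How many planned subjects the discrepancy touches.** Each adjuvanted formulation has two subgroups (needle and needleless), so 2 × 65 = 130 subjects.

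- Compared as sets, 10 mg is common and one formulation differs: 2 of 6 subgroups, 130 of 390.
- Paired in order, the lower arm is 5 mg against 10 mg and the higher is 10 mg against 20 mg. Both differ, each by a factor of 2 (10/5 and 20/10): 4 of 6 subgroups, 2 × 130 = 260 of 390.

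The text does not say how the arms correspond, so 130 is the lower figure and 260 the upper.

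**Step 5. What the intended arms can compare.** With 0, 5 and 10 mg, the randomised contrasts are 0 v 5, 0 v 10 and 5 v 10 mg. None involves 20 mg. At the planned group size, adding a 20 mg arm would make 4 formulations × 2 devices = 8 groups, and 8 × 65 = 520 subjects, above the ceiling of 400.

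**The case against.** The best defence is that this is a correctable slip in the text. Three places give 5 mg and 10 mg. Section 9.10 offers only an open-ended example, so 7.2 carries the contradiction almost alone. Section 7.4 says that adjuvant is mixed under the vaccine administration SOP, and section 9.10 says that allocation comes through an on-line system. Neither is shown, and both may carry the right doses. Section 1.2.3 also regards 5 to 20 mg as safe. All of this limits the harm, but it does not reconcile the sections.

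A reader might infer more than the text supports:

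- **Every adjuvanted subject would receive double the dose.** This holds only if the arms are paired in order. As sets, 10 mg is common to both.
- **The 5 mg arm is a violation as written.** That reads 7.2 alone. Taken literally, 5, 10 and 20 mg are all shown somewhere in the protocol, so 7.8.1 becomes ambiguous but does not plainly rule out 5 mg.
- **Staff will prepare the wrong doses.** This cannot be concluded without seeing the SOP.
- **The trial cannot meet its dose aims.** Section 1.1 speaks of wanting to "thereby identify the minimum adjuvant dose required for maximal vaccine enhancement" and to "confirm whether the reduced adjuvant dose delivers an equivalent anti-influenza antibody response". This is rationale text, and no stated objective, endpoint or decision rule depends on it. The primary objective is a comparison with TIV alone. The benefits in section 1.2.3 can be read as improvement over unadjuvanted vaccine, which is testable here. Under the plateau premise of section 1.2.2, similar responses at 5 mg and 10 mg would give indirect support for the lower dose. What remains true is that no randomised comparison with 20 mg exists within this trial.
- **A non-significant difference between doses will be taken as equivalence.** The protocol nowhere says so. Section 9.3 describes the analysis as descriptive, and section 9.4 provides geometric mean titres with 95% confidence intervals.

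**Conclusion.** The contradiction is real, and the protocol does not resolve it. Sections 7.2 and 9.10 state the wrong adjuvant doses, and 5.2 states the intended ones. At least one adjuvanted formulation is discrepant (130 of 390 planned subjects), and both are if the arms are paired in order (260 of 390). The counts rest on 65 subjects in each of 6 groups, as section 9.7 plans. The judgement about which text is wrong rests on the protocol's own account of 20 mg as the earlier dose.

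Severity is minor. The intended doses can be worked out from the document, and the design and sample size do not depend on the slip. The comparison with TIV alone is unaffected once 5.2 governs. Until then the doses in the test arms, and so the exposure behind the primary safety endpoint, are not stated consistently.

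The rationale aims in sections 1.1 and 1.2.3 merit an optional wording note only: the direct comparison between adjuvant doses is 5 mg v 10 mg, and nothing about 20 mg can be shown by randomised comparison in this trial.

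**What to change.** 1. In section 7.2, replace 10 mg or 20 mg with 5 mg or 10 mg.
2. In the example in section 9.10, make the same replacement.
3. Check that the vaccine administration SOP and the on-line randomisation system both carry 5 mg and 10 mg.
4. Optional: in sections 1.1 and 1.2.3, say that 5 mg and 10 mg are each compared with TIV alone and with each other, and that the trial contains no randomised comparison with 20 mg.

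The cost is one wording amendment and a check of two operational sources. Section 11.3 requires ethics approval for major amendments, and the closing statement on amendments requires it for all, so the correction should be planned as needing approval. No arm, subject or test is added. A 20 mg arm is not needed to resolve this point and, at 520 subjects, would exceed the recruitment ceiling.
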